### **13.4 Study Stopping Rules**

This study may be terminated by the PI, IRB, Safety Monitor or FDA at any time. Reasons for terminating the study may include the following:

- ☐ The incidence or severity of AEs in this or other studies indicates a potential health hazard to subjects.
- ☐ Subject enrollment is unsatisfactory.
- ☐ Data recording is inaccurate or incomplete.
- ☐ Adverse events which may result in study termination include, but are not limited to:
  - Death
  - Cancer
  - Serious infection
  
  - Anaphylaxis
  - Acute hepatic failure
- ☐ ≥ 2 patients develop the same CTCAE Grade 3.
- ☐ 1 patient develops a CTCAE Grade 4 or higher.

### **13.5 Reporting of Serious Adverse Events**

#### **Study Sponsor Notification by Investigators**

An SAE must be reported to the study Sponsor by telephone or fax (preferred) within 24 hours of the event. An SAE Form must be completed by the Investigator and faxed to the study Sponsor within 24 hours. The Investigator will keep a copy of this SAE form on file at the study site. Report SAEs by phone and fax to:

[name], MS [contact] (telephone)  
[contact] (fax)

At the time of the initial report the following information should be provided:

- |                                                     |                                                                                                           |
|-----------------------------------------------------|-----------------------------------------------------------------------------------------------------------|
|  Study Identifier           |  Whether study treatment was discontinued                                         |
|  Study Center               |  The reason why the event is classified as serious                                |
|  Subject Number             |  Investigator assessment of the association between the event and study treatment |
|  A description of the event |                                                                                                           |
|  Date of onset              |                                                                                                           |
|  Current Status             |                                                                                                           |

Within the following 48 hours, the Investigator must provide further information on the SAE in the form of a written narrative. This should include a copy of the completed SAE Form, and any other diagnostic information that will assist the understanding of the event. Significant new information on ongoing SAEs should be provided promptly to the study Sponsor.

### **IRB Notification by Investigators**

Reports of all SAEs (including follow-up information) must be submitted to the IRB within 10 working days if it falls under the UPIRTSO guidelines (unexpected and related to study drug). All deaths, regardless of expectedness or causality, must be reported to the IRB within 10 working days. Copies of each report and documentation of IRB notification and receipt will be kept in the Clinical Investigator's binder.

### **FDA Notification by Sponsor**

The study Sponsor shall notify the FDA by telephone or by fax (preferred) transmission of any unexpected SAE associated with the use of the study drug for which the Investigator holds an active IND as soon as possible but no later than 7 calendar days from the Sponsor's original receipt of the information.

If a previous AE that was not initially deemed reportable is later found to fit the criteria for reporting, the study Sponsor will submit the AE in a written report to the FDA (as applicable) as soon as possible, but no later than 15 calendar days from the time the determination is made.

### **UPIRTSO Events**

Investigators are required to submit a report of UPIRTSO events to the IRB within 10 working days of first learning of the event.

### **Pregnancy**

If a female subject becomes pregnant during the study, she will be withdrawn from the study immediately. Though pregnancy is not by definition an SAE, it will be subject to SAE reporting requirements described in Section 13.5.

Though the subject will be withdrawn from the study, permission to record survival and adverse event (malignancy, hospitalization for infection) data for the mother to the end of the pregnancy and of survival data for the baby at birth will be requested.

## **14.0 Withdrawal of Subjects**

Subjects will be encouraged to complete the study; however, they may voluntarily withdraw at any time. If a subject is withdrawn prior to study completion, attempts will be made to schedule and conduct an Early Termination visit for medical assessment. If a subject cannot be contacted after 5 telephone calls and 3 letters/emails, they will be considered lost to follow-up.

Subjects who discontinue study medication (e.g. due to non-compliance, AEs, etc.) will be asked to remain in the study for follow-up per the study schedule to preserve the ability to perform an intent to-treat (ITT) analysis. If a subject or their legal guardian (as applicable) withdraws consent to participate in the study, attempts will be made to obtain permission to record survival and adverse event (malignancy, hospitalization for infection) data at the Week +44 study point.

Study drug will be discontinued in any subject meeting the following criteria for drug-induced liver injury:

- ☐ ALT or AST > 8x upper limit of normal (ULN)
- ☐ ALT or AST > 5x ULN for more than 2 weeks
- ☐ ALT or AST >3x ULN and (total bilirubin >2x ULN or INR > 1.5)
- ☐ ALT or AST >3x ULN with the appearance of fatigue, nausea, vomiting, right upper quadrant pain or tenderness, fever, rash, and/or eosinophilia (>5%)

Management of suspected drug-induced liver injury will be consistent with the FDA Guidance for Industry Drug-Induced Liver Injury: Premarketing Clinical Evaluation. Specifically, an increase of ALT or AST of >3x ULN will be followed by repeat testing within 48-72 hours of ALT, AST, alkaline phosphatase, and total bilirubin level. There will be inquiry made about symptoms. If symptoms persist or repeat testing shows ALT or AST >3x ULN close observation to determine whether the abnormalities are improving or worsening will be initiated as follows:

- ☐ Repeating liver enzyme and serum bilirubin tests two or three times weekly. Frequency of retesting can decrease to once a week or less if abnormalities stabilize or the trial drug has been discontinued and the subject is asymptomatic.
- ☐ Obtaining a more detailed history of symptoms and prior or concurrent diseases.
- ☐ Obtaining a history of concomitant drug use (including nonprescription medications and herbal and dietary supplement preparations), alcohol use, recreational drug use, and special diets.
- ☐ Ruling out acute viral hepatitis types A, B, C, D, and E; autoimmune or alcoholic hepatitis; NASH; hypoxic/ischemic hepatopathy; and biliary tract disease.
- ☐ Obtaining a history of exposure to environmental chemical agents.
- ☐ Obtaining additional tests to evaluate liver function, as appropriate (e.g. INR, direct bilirubin).
- ☐ Considering gastroenterology or hepatology consultations.

Study drug will be discontinued in any subject developing one of the following:

- Serious infection (e.g. cellulitis, pneumonia requiring hospitalization, or bone and joint infections, from fungal, mycobacterial and bacterial pathogens; fungal sinusitis)
- Malignancies (e.g. Lymphomas, breast, respiratory, and digestive system cancers)
- Severe hypersensitivity reactions including anaphylactic reactions and angioedema

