| Sleep Diary – parent assessment x 1 week               |           | X h                  | X                 |                                                              | X                                | X                                      |
| Stooling Survey                                        |           | X                               | X                 |                                                              | X                                | X                                      |
| Safety labs (CBCD, BMP, LFT, lipid panel) i | X         | X                               | X                 | X                                                            | X                                | X                                      |
| Thyroid studies                                        | X         |                                 |                   |                                                              |                                  |                                        |
| Blood biomarkers                                       |           | X                               | X                 |                                                              | X                                | X                                      |
| Urine biomarkers                                       |           | X                               | X                 |                                                              | X                                | X                                      |
| Stool collection                                       |           | X                               | X                 |                                                              | X                                | X                                      |
| Genetic biomarkers (optional)                          |           | X                               | X                 |                                                              | X                                | X l                         |
| CSF collection (optional)                              |           | X                               | X                 |                                                              | X                                | X (week 44 only)                       |

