### **10.4 Laboratory Evaluations**

Blood and urine will be collected at the time points described in the Schedule of Events.

Complete blood count with differential (CBCD), liver function tests (LFTs), lipid panel, and basic metabolic panel (BMP) will be performed at Quest Diagnostics or LabCorp at Screening, Week -8, Day 1, Week +2, Week +4, Week +8, Week +12, Week +16, Week +20, Week +24 (only if dose increased at week +16), Week +36, and Week +44. Thyroid function tests (TSH, Free T4) and Quantiferon-TB Gold test will be obtained at Screening.

Anti-anakinra antibodies will not be measured during this pilot study; the rationale for this is based on prior studies showing no effect of anti-anakinra antibodies on pharmacokinetic (PK) parameters, efficacy outcomes or adverse events (AEs) and low incidence of neutralizing anti-anakinra antibodies. However, serum will be collected at Day 1, Week +8, Week +36, and Week +44 and stored for possible future testing of anti-anakinra antibodies if needed for interpretation of safety or efficacy results.

Plasma will be collected and stored for future PK studies at Day 1, Week +8, Week +36, and Week +44.

For post-menarche female patients, a urine pregnancy test will be performed at Screening and at each study visit.

Plasma, serum, urine, and PAXgene tube for RNA will be collected for future biomarker studies at Week -8, Day 1, Week +8, Week +16, Week +36, and Week +44. Consent will be requested to perform these additional biomarker studies on

stored samples in the future as well as genome wide association studies (GWAS) and/or large-scale genomics/transcriptomics assays such as sequencing, methylation and expression.

Buffy coat for DNA will be collected for future biomarker studies at Week -8, Day 1, and Week +36.

Stool will be collected at Week -8, Day 1, Week +8, Week +16, Week +36, and Week +44 for future microbiome studies.

Whole blood will be collected at Week -8, Day 1, Week +8, Week +16, Week +36 and Week +44.

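### Section 14.0 makes INR above 1.5 with ALT or AST above 3x ULN a mandatory stop, but neither test panel it fixes after such a rise includes INR

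*Protocol*

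**What the plan says.** All the liver rules are in Protocol Section 14.0. The stop is compulsory: "Study drug will be discontinued in any subject meeting the following criteria for drug-induced liver injury". Four criteria follow, and the one at issue begins "ALT or AST >3x ULN and (total bilirubin >2x ULN or INR > 1.5". Its two arms, bilirubin and INR, are joined by an or and carry equal force.

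The same section then sets out what is measured once ALT or AST passes 3x ULN.

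- **First step:** "repeat testing within 48-72 hours of ALT, AST, alkaline phosphatase, and total bilirubin level".
- **Second step, conditional:** "If symptoms persist or repeat testing shows ALT or AST >3x ULN close observation" is to begin, and its first item is "Repeating liver enzyme and serum bilirubin tests two or three times weekly".
- **Later in the close-observation list:** "Obtaining additional tests to evaluate liver function, as appropriate (e.g. INR, direct bilirubin". This is the only provision for measuring INR anywhere in the protocol.

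The routine labs are described in Section 10.4, "Complete blood count with differential (CBCD), liver function tests (LFTs), lipid panel, and basic metabolic panel (BMP) will be performed", and in the Section 10.2 schedule as "Safety labs (CBCD, BMP, LFT, lipid panel". Neither place names INR or any coagulation test.

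**The concern.** A criterion that compels action should rest on a measurement that is also compelled. Here the bilirubin arm is always evaluated after a rise above 3x ULN, because both fixed panels carry bilirubin. The INR arm is evaluated only if someone chooses to order the test, and the text raises that choice only once close observation has started.

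At stake is a participant with ALT or AST above 3x ULN, INR above 1.5 and bilirubin not above 2x ULN. Under Section 14.0 this participant must come off anakinra. If INR is not ordered, nobody knows the criterion is met and dosing continues without any departure from the written procedure.

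The other main safeguard in the lower enzyme range is the symptom criterion. Several of its items, such as fatigue, nausea and abdominal pain, depend partly on self-report. The trial admits children with significant CNS impairment (Section 5.2) and measures pain with a checklist designed for children with severe cognitive impairment (Section 10.9). It is reasonable to infer that an objective laboratory value counts for more in this population, although the protocol offers no data on the point.

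**Working it through.** The point involves no sample size, power or event-rate calculation, and the plan has no figure to reproduce. The check sets the stopping criteria beside each test list.

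**Step 1. Where each arm of the criterion is measured**

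| Test list | Bilirubin | INR |
|---|---|---|
| Stop criterion at >3x ULN (Section 14.0) | yes, >2x ULN | yes, >1.5 |
| 48-72 hour retest (Section 14.0) | yes | no |
| Repeat tests under close observation (Section 14.0) | yes | no |
| Additional liver tests under close observation (Section 14.0) | direct bilirubin, by judgement | by judgement |
| Scheduled safety labs (Sections 10.2 and 10.4) | not itemised, within LFTs | not named |

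INR is thus in 1 of the 4 liver stopping criteria, 0 of the 2 fixed panels and 1 discretionary item. Its only other appearance is in the abbreviation list, so the document mentions it 3 times in all.

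**Step 2. Whether the scheduled labs fill the gap**

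Section 10.4 lists Screening, Week -8, Day 1 and Weeks +2, +4, +8, +12, +16, +20, +24, +36 and +44. That is 3 + 9 = 12 time points. Week +24 applies only if the dose rose at Week +16, so 12 - 1 = 11 apply to everyone. INR is named at none of them.

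The protocol does not define the components of the LFT panel. I take INR to be outside it, because Section 14.0 itself treats INR as an additional test.

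**Step 3. When INR alone decides**

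Take bilirubin at or below 2x ULN, no listed symptom and no eosinophilia above 5%. What remains of the four criteria is:

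| ALT or AST | Stop that applies without INR | Is INR the only value that can compel a stop now? |
|---|---|---|
| >8x ULN | immediate | no |
| >5x to ≤8x ULN | after more than 2 weeks above 5x | yes, for at most 2 weeks |
| >3x to ≤5x ULN | none | yes, with no time limit |

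**Step 4. Whether the lower band can be occupied**

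The liver thresholds in Section 5.3 exclude AST or ALT above 5x ULN, or above 3x ULN with bilirubin above 2x ULN. A child with ALT between 3x and 5x ULN and bilirubin at or below 2x ULN is not excluded by those numbers, although the investigator may exclude on general grounds. The band can therefore be occupied at entry as well as reached on treatment. The protocol gives no rate for either, so I attach no probability.

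**The case against.** The strongest reply is that INR is not absent. It is one of only two tests named as examples in the close-observation list. An investigator who is told to stop on INR above 1.5, and shortly afterwards is told INR may be obtained, has an obvious reason to order it. The two provisions do not contradict each other. This stands to the extent that it would be wrong to say INR is never measured or that the criterion cannot be applied. It does not close the gap, because the measurement remains optional and is not raised until the retest has led to close observation.

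A second reply is that Section 14.0 commits to managing suspected liver injury in line with an FDA guidance, which may require more than the listed steps. That guidance is not available here. However, the protocol goes straight from that commitment to its own specific procedure, and the panel it specifies omits INR.

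A third reply is that other safeguards remain. A laboratory abnormality that prompts further tests is an adverse event under Section 13.2. Under Section 27.7 a grade 3 event cuts the dose by 50 mg, and drug is stopped if the event has not resolved within 2 weeks. The symptom criterion is also broad. All of this narrows the affected group. The dose-reduction rule, however, depends on adverse-event grade and does not cause INR to be measured, so it cannot stand in for the INR criterion.

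Finally, how often to repeat INR is partly a matter of clinical preference. I accept that. Including it once in the first retest is the more important half of the proposal.

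**Conclusion.** The concern holds. Section 14.0 makes a mandatory stop depend on a test that the same section leaves optional, and neither of its two fixed panels supplies the value.

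The effect is small. It is confined to participants with ALT or AST above 3x and up to 8x ULN, bilirubin not above 2x ULN, no listed symptom and no eosinophilia above 5%, for whom the investigator does not order INR. Between 5x and 8x ULN the exposure is limited to 2 weeks; between 3x and 5x ULN the liver criteria set no limit. In a study of 20 participants few, if any, may fall in this group, and the protocol gives no figure from which to say how many.

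The conclusion rests on one assumption, that the undefined LFT panel does not include INR, which the wording of Section 14.0 supports. This is a worthwhile safety clarification, not a flaw in the design or analysis.

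**What to change.** In Section 14.0, add INR to the tests repeated at 48-72 hours, and repeat it with the close-observation draws for as long as ALT or AST stays above 3x ULN and study drug continues. The stopping thresholds and the scheduled safety panels can stay as they are.

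The cost is one line of protocol text plus one extra assay, and possibly one extra tube, on draws that are already required. It applies only to the few participants whose ALT or AST exceeds 3x ULN.

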## **15.0 Risks to Subjects**

### **15.1 Venipuncture**

The risks of venipuncture are transient pain, bleeding, lightheadedness, bruising, possible vasovagal reaction, and infection. Only trained certified nursing assistants, nurses, nurse practitioners, or physicians will be allowed to perform venipuncture to minimize the risk of complication.

### **15.2 Anakinra**

The following have been reported as adverse reactions related to anakinra in other studies:

- Serious infections (e.g. Cellulitis, pneumonia, sinusitis, upper respiratory tract infections, ear infections, nasopharyngitis, gastritis, bone and joint infections, from fungal, mycobacterial and bacterial pathogens)
- Injection-site reactions (e.g. Erythema, ecchymosis, inflammation, and pain)
- Malignancies (e.g. Lymphomas, breast, respiratory, and digestive system cancers)
- Hematologic events (e.g. Decreased total white blood cell counts, neutropenia, eosinophilia, thrombocytopenia, epistaxis)
- Hypersensitivity reactions including anaphylactic reactions, angioedema, urticaria, rash, and pruritis
- Immunogenicity (i.e. Anti-anakinra binding antibodies)
- Headache, dizziness
- Nausea, diarrhea, abdominal pain
- Arthralgia
- Flu-like symptoms; pyrexia, malaise

## **16.0 Potential Benefits to Subjects**

Subjects will be treated with anakinra. These treatments have potential direct benefits to the subjects. These potential direct benefits include, but are not limited to, improved behavior, sleep, stooling, communication, mood, and gait; as well as decreased seizure frequency, disordered movement and fatigue.

## **17.0 Sharing of Results with Subjects**

**17.1** Individual subject safety laboratory results that are clinically significant, as determined by the study PI, will be shared with subject's parent/guardian and the subject's primary care physician by email or phone/fax if email is not available. Confirmation of receipt of these results will be required either by email or phone call.

**17.2** At the end of the study (Week +44), all results will be given to subjects/parents/guardians upon request.

## **18.0 Setting**

Study visits will take place at the LI Clinical and Translational Research Center (CTRC).

## **19.0 Resources Available**

This study will be conducted by the Rare Disease Clinical Research Group (RDCRG) at LI. This group includes four physicians, two study coordinators, one regulatory specialist, and one program coordinator, who all have previous experience conducting clinical research in MPS and other rare disease, pediatric and adult, populations. They are thus knowledgeable of the local study site, culture, and society. All are current with their education/training requirements for conducting research in human volunteers.

The CTRC provides support and resources for studies on human research participants. Research nursing within the CTRC integrates high quality patient care, patient-oriented research, and education. CTRC nurses support protocol implementation and the research subject's participation in clinical trials. They provide skillful nursing care, expertise in protocol implementation and data collection. The nurses have diverse backgrounds, experiences, and they hold certifications in a variety of specialized areas such as bone densitometry, cardiac monitoring, and advanced cardiac life support.

All study personnel interacting with subjects are certified in the conduct of clinical trials, good clinical practice, the protection of human subjects, and HIPAA regulations to assure compliance with regulatory requirements. They are also trained to ensure that research participants are fully informed about the details of their research protocol visits, protection of private medical health information, and the Research Subject's Bill of Rights.

To assist the investigator and the research subject during the consenting process and on follow-up visits, several of our staff members can provide translation in Spanish, Tagalog, and other languages. The outpatient unit contains nine exam rooms (3 with hospital beds), 2 consultation rooms, and 1 multipurpose room.

Medical or psychological resources are available through Harbor-UCLA Medical Center.

The PI meets on a weekly basis with the RDCRG and will conduct an in-service training session with CTRC staff to ensure that all persons assisting with the trial are adequately informed about the protocol, the investigational product, and their trial-related duties and functions.

Funding for this study will be provided by the Cure Sanfilippo Foundation. Study drug will be provided by Sobi. The UCLA CTSI Grant UL1TR001881-01 will provide partial funding for costs related to utilization of CTSI facilities and resources.

